**Fig. 1 Fig1:**
[figure not shown]
Flow chart of study participation. *A subset of participants who complete T3 feedback will be invited to complete an in-depth interview and questionnaires regarding the visualizations following trial completion

EMA will consist of repeated self-report measures of emotions and somatic symptoms, social experience such as interactions with peers, avoidance, context (e.g., family, friends, home, school attendance), and sleep duration/quality. Questions include a mix of visual analogue scales, free response, and interval or nominal checkboxes. Participants will complete the EMA for 7 consecutive days (3 prompts/day, at morning, afternoon, and evening using a fixed time-based sampling method employing a coverage model (e.g., asking about the time since the last prompt)) using the *CareTeam* platform, developed and deployed by our industry partner [34]. EMA procedures will be set up using established best practices for use in children and adolescents [39, 40] and previously used measures in a pediatric anxiety sample [7]. The development of the EMA platform was pilot tested with youth, trainees, and investigators, and integrated preliminary feedback from a concurrent initiative we are developing that is soliciting feedback from patients and families regarding the development of an in-home data collection platform [38].

After completion of each phase, youth will be asked to evaluate their experience with the EMA (and, at the end of Phase B, the data visualization) with an investigator-created questionnaire; see Additional file 3. A subset of youth will be invited to take part in an interview at the end of the trial to provide more in-depth feedback on the visualization platform.

#### Informed consent

Consent (from parent/legal guardian) and assent (from youth) will be obtained. Potential participants will be contacted by email by a researcher (not involved in their clinical care), introducing the study with an invitation letter and consent form, and providing the opportunity for the family to opt out. The researcher will follow up a week later to see if the family is interested in participating. If so, the researcher will review the consent form with the parent and youth over the phone and send them the link to complete the e-consent forms using REDCap, a secure online system hosted by the BC Children’s Hospital Research Institute [41].

#### Confidentiality

All research data will be identified using a specific code number assigned to each participant. Any personally identifying information (e.g., name, date of birth) will not be included on any research record that has the participant’s code number. The master list of participants and their corresponding codes will be kept in a password-protected file on a secure server and will have limited access. No information with personal identifiers will be released to outside agencies during or after the study without written consent from participants. Any phones borrowed by study participants will be restored to factory settings upon return to eliminate any possibility of the identity of participants becoming known to others that may use the phone.

Only those directly involved in the study will have access to study data, including the Principal Investigator, Co-Investigators, and any research assistants or trainees added to the project. All e-consent/assent forms and questionnaires will be collected using the secure, web-based application, Research Electronic Data Capture (REDCap), via the BC Children’s Hospital Research Institute Clinical Research Support Unit. *CareTeam* [34], which is the platform that will be hosting the EMA questions and visualizations, accesses aggregate data in an ongoing capacity for metrics and only access individual data if providing support to a specific user for a technical problem.

#### Baseline assessment

The following domains will be assessed prior to randomization at the baseline period:Demographics and contextual factors: Youth will self-report their assigned sex and gender identity [42], health, and medication/treatment use. Youth will report on pandemic-related stressors using the *COVID-19 Impact Questionnaire* (adapted by Kopala-Sibley, Noel & Birnie at the University of Calgary, from impact measures of natural disasters on mental health [43], which assesses financial, health, social, occupational, and academic impacts of the pandemic. This measure does not contain items that directly overlap with mental illness to prevent inflated associations with anxiety measures.Pain characteristics and interference: Youth will provide reports of pain duration, pain intensity, and interference (using the *PROMIS* (Patient-Reported Outcomes Measurement Information System ®) pain scales [44, 45]).Anxiety and depression symptoms: Youth will provide reports of symptoms of anxiety and depression using the *PROMIS* Emotional Distress scales [46, 47].Somatic symptoms: Reports of youth’s somatic symptoms will be provided by youth using the well-validated *Children’s Somatic Symptoms Inventory-8 item version* [48]*.*

### Randomization

#### Sequence generation

The sequence of randomization to assign participants to start with either Part A (EMA) or Part B (EMA + data visualization) will be generated by the investigators using computer-generated random numbers with a 1:1 allocation ratio. No blocking or stratification will be used.

#### Concealment mechanism

Allocation sequence will be implemented using sequentially numbered, opaque, sealed envelopes.

#### Implementation

A research assistant, who was not involved in the sequence generation and does not have access to the randomization list, will enrol participants and assign them to interventions based on the next assigned envelope.

#### Blinding

Data analysts will be blinded to participant allocation. The only exception to this will be the qualitative analysis of the questions regarding satisfaction, etc., of the visualization platform, as this question will only be asked after participants complete Part B. Due to the nature of the study, participants and care providers will not be blinded.

### Interventions

#### Explanation for the choice of comparators

Comparing the EMA + visualization to EMA alone will allow us to determine the effect of self-monitoring by collecting data alone compared to the effect of “seeing” visualized data.

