### Procedures

Complete procedures are outlined in Fig. 1. Consent and assent for all participants will be obtained from youth and parents/caregivers. Youth will complete baseline questionnaires prior to randomization. Once participants have been assigned to groups, the smartphone-administered EMA data collection will be completed by the youth for two 7-day periods with a 7-day break in between (washout period). Participants who do not have access to a smartphone will be loaned a pre-paid, data-enabled smartphone for the duration of the study.^2^ The trial will utilize an A-B crossover design in which participants will be randomly assigned to receive either Part A (EMA alone) or Part B (EMA plus visualization) first and then receive the opposite phase after the 7-day break. In Part A, the data collection will occur through EMA (repeated self-report via smartphone). In Part B, the data visualization will appear immediately after data entry, updating as new data is added and allowing the participant to interact with their data as the visualizations change throughout the week. Youth will be oriented with basic instructions on how to navigate the visualization platform, what the visualizations represent, and how to interpret them.

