#### Relevant concomitant care permitted or prohibited during the trial 

Participants will be encouraged to continue to engage in any other treatments for their chronic pain concurrently with trial participation. As the 3P approach to chronic pain management (combination of physical, psychological, and pharmacological therapies) is the standard of care, it was concluded to be unethical to stop or delay any of these treatments during the trial. Indeed, the intention of the data visualization intervention would be to supplement or support other therapies; therefore, the concurrent use of additional interventions was deemed to be the most ecologically valid and ethical approach. Participants will be asked to report the use of any concurrent interventions during the trial at baseline and during each feedback questionnaire.

Two additional measures have been put in place to provide support to participants during the trial. Resources for pain and mental health care are included on the consent and assent forms for participants to reference. Additionally, during EMA assessment periods, the participant will receive a prompt at the end of each day to try a free self-management application (*Rootd*; www.rootd.io). *Rootd*’s content is based on cognitive behavioral therapy and includes lessons on understanding and managing anxiety in the short and long term, a journal tool, exercises, and step-by-step guides to strategies such as deep breathing and active visualization. The app also features an emergency contact button to call a loved one or hotline if in distress and a Personal Stats Page to track user progress.

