#### Secondary outcomes

Relationships between daily measured variables will be assessed by examining the data collected through the EMA, as described above. This data will also be examined to determine preliminary differences between Part A and Part B.

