#### Secondary outcomes

Multi-level modeling will be employed to account for the nested nature of the data and accommodate any missing data, examining patterns of association between variables (both concurrent and time-lagged) at the within- and between-participant level. Previous reports have indicated that a sample size of 50 is sufficient to conduct such analyses [13]. Specifically, we will examine whether stressful events (e.g., negatively perceived peer interactions) and avoidance at time 1 predict somatic and pain symptoms at time 2, moderated by anxiety. Qualitative content analysis will be used to summarize common themes reported by participants regarding the effectiveness of the visualization application based on their feedback provided in the follow-up questionnaire. Data gathered through the EMA over the length of the study will also be quantitatively analyzed to check for clinical improvement following Part A and Part B.

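### The crossover identifies only the added effect of visualization over EMA, but the comparator rationale claims more and the stated check for improvement after each part is uncontrolled

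*Protocol article*

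**What the plan says.** All references are to the protocol article.

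- **Explanation for the choice of comparators.** The comparison of the two parts "will allow us to determine the effect of self-monitoring by collecting data alone compared to the effect of “seeing” visualized data".
- **Procedures.** Participants are "randomly assigned to receive either Part A (EMA alone) or Part B (EMA plus visualization) first" and cross over after a 7-day break. Each part is 7 days of EMA, and no arm or measured period is without it.
- **Relevant concomitant care.** In both parts, "during EMA assessment periods, the participant will receive a prompt at the end of each day to try a free self-management application". The app (Rootd) is based on cognitive behavioral therapy and has its own progress-tracking page. In addition, "Participants will be encouraged to continue to engage in any other treatments for their chronic pain concurrently with trial participation". Concurrent care is recorded: "Participants will be asked to report the use of any concurrent interventions during the trial at baseline and during each feedback questionnaire".
- **Outcomes, Secondary outcomes.** Of the EMA data: "This data will also be examined to determine preliminary differences between Part A and Part B".
- **Data analysis, Secondary outcomes.** The EMA data "will also be quantitatively analyzed to check for clinical improvement following Part A and Part B". This is the only quantitative check of symptom benefit in that section. The multi-level models described there concern associations between variables.
- **Status of these analyses.** The design is called exploratory (Study design), analyses of intervention impact are called preliminary and intention-to-treat (section on non-adherence and missing data), and the primary outcomes are feasibility measures.

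**The concern.** Two statements go beyond what the design can support.

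First, the comparator rationale speaks of determining an effect of self-monitoring as well as an effect of seeing the data. An effect of self-monitoring needs a condition without it, and there is none. Part A is also not EMA on its own in practice: it comes with a daily prompt to a self-management app and with continued treatment.

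Second, the analysis section checks for improvement after each part and names no reference condition. Youth recruited from a pain service may change over a week for many reasons unrelated to EMA or the dashboard. The randomized comparison that would deal with this appears under outcomes as an A-B difference, but the analysis section does not carry it through as the effect analysis.

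At stake is how the pilot's symptom data can be read. The abstract promises pilot data on symptom improvement linked to engagement with the platform, and the objectives ask whether interacting with visualized data can be effective. A per-part change answers neither question. The decision on a larger trial is less exposed, because the article rests it on feasibility and acceptability.

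**Working it through.** **The article's own figure.** The only precision figure given is the interval for 80% retention with 50 participants. Wald: 0.80 ± 1.96 × √(0.80 × 0.20 / 50) = 0.80 ± 0.111, that is 68.9% to 91.1%. This reproduces the stated 69–91%. The present point does not depend on it; 80% of 50 gives the 40 completers used below.

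**What each quantity contains.** Let *e* be the effect of EMA, *v* the added effect of visualization, and *c* everything else common to both parts (Rootd, ongoing care, natural course, regression to the mean).

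- Change over Part A = *e* + *c*
- Change over Part B = *e* + *v* + *c*
- Part B minus Part A = *v*

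The terms *e* and *c* only ever appear as a sum, so no analysis of these data separates them. The difference *v* is identified, provided that use of Rootd and other care does not differ by part and nothing carries over the break.

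**Period term.** If the second period differs from the first by π, B minus A is *v* + π for participants who start with A and *v* − π for those who start with B. The unadjusted mean is then *v* + π × (n_AB − n_BA)/N. Randomization is unblocked, so the two sequences can differ in size by chance. The residual is zero on average, and a period term removes it in the trial actually run.

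**Size, under assumptions.** The article gives no figure for shared change and specifies no per-part test. Assume no effect of EMA or the dashboard (*e* = *v* = 0) and a two-sided one-sample t-test at 5%. The chance of significance comes from the noncentral t with n − 1 degrees of freedom and noncentrality s√n, where s is the shared change in SDs of the within-person change. For n = 40 and s = 0.2, the noncentrality is 0.2 × √40 = 1.26, which gives 24%.

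| Shared change (SD of within-person change) | n = 40 | n = 50 |
|---|---|---|
| 0 | 5% | 5% |
| 0.2 | 24% | 28% |
| 0.3 | 46% | 55% |
| 0.5 | 87% | 93% |

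The scale matters. Now express the change as a linear drift over the week in units of the total SD of a single rating. Assume an ICC of 0.5, residual variance split equally between day and prompt (0.25 each), and a test of the last 6 against the first 6 of 21 prompts.

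- Each 6-prompt mean covers 2 days, so the variance of the difference is 2 × (0.25/2 + 0.25/6) = 0.333, SD 0.577.
- The two sets of prompts lie 15 of 20 steps apart, so 0.75 of the drift is seen.
- A drift of 0.2 total SD is therefore 0.75 × 0.2 / 0.577 = 0.26 on the first scale.

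Simulation on this second scale (4,000 trials per cell) gave:

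| Shared drift (total SD) | n = 40 | n = 50 |
|---|---|---|
| 0.2 | 36% | 44% |
| 0.3 | 68% | 77% |
| 0.5 | 98% | >99% |

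**The randomized contrast.** In 20,000 simulated crossovers per setting (40 participants, simple randomization, shared change 0.3 or 0.5, period effect 0 or 0.3 SD), B minus A averaged about 0 and was significant in 5.1% to 5.3% of runs, with or without period adjustment. In the second-scale simulation the period-adjusted contrast was significant in 4.6% to 5.5%.

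**The case against.** The strongest reply is that the valid contrast is already there. The comparator sentence opens with the B-versus-A comparison and goes on to set one effect against the other. It sits under choice of comparators, and no objective elsewhere seeks a stand-alone effect of EMA. The outcomes section names A-B differences, in which Rootd and usual care cancel. This stands in large part: the rationale is loosely worded rather than a commitment to estimate EMA alone. It still names an effect of self-monitoring as something that will be determined, and the analysis section still states the per-part check rather than the contrast.

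A reader might infer more: that change shared by both parts would be credited to EMA or the dashboard. The article does not say so. It calls the analyses preliminary and records concurrent care; the attribution would arise only if per-part change were read causally. Nor do Rootd and ongoing care confound the A-B difference, unless their use differs by part or their effect carries over.

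The objection to the numbers also stands. The per-part test and the size of the shared change are assumptions, and it is close to self-evident that a test for change detects change put in. The rates show only that such a test cannot tell shared change from benefit.

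Finally, the exact model is ordinary detail for an analysis plan, and its absence is not the complaint. The complaint is that the check that is stated is the wrong one for an effect.

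**Conclusion.** The point holds in limited form. With EMA, Rootd prompts and ongoing care in both parts, the crossover identifies only the added effect of visualization over EMA. The comparator rationale is too broad, and the check for improvement after each part is, as worded, an uncontrolled change that supports no statement about EMA or the dashboard. This conclusion follows from the structure of the design and needs no assumed figure.

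The size is illustrative. Under a shared change of 0.2 to 0.5 SD and no true effect, a per-part test in 40 completers is significant in about 24% to 87% of trials on one SD scale and 36% to 98% on the other, against about 5% for B minus A. That last figure rests on equal use of shared care in both parts and no carry-over.

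Severity is minor to moderate: the analyses are secondary and exploratory, feasibility is primary, and the A-B difference is already named as an outcome.

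**What to change.** 1. **Data analysis, Secondary outcomes.** Replace the check after each part with the within-participant Part B minus Part A difference in EMA-reported symptoms, with a period term and a 95% CI, as the only preliminary effect estimate. Report change within each part as descriptive, not as evidence of benefit.
2. **Explanation for the choice of comparators.** State that the comparison gives the added effect of visualization over EMA, with Rootd prompts and usual care in both parts. Drop the claim to determine an effect of self-monitoring.
3. **Optional.** Summarize Rootd use by part, if the feedback questionnaire captures it; that questionnaire is in an additional file not seen here. This would help to judge whether use was balanced.

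The cost is rewording in two sections and a small change of analysis, using data already collected. No participants, visits or measurements are added. What is given up is a claim about EMA alone that no result of this design could support.

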#### Intervention description

The intervention is described in detail in the “Materials” section above. Briefly, the intervention will involve access to the data visualization dashboard, where participants can view visualizations of the data they are inputting in the EMA to observe trends and interactions of different dimensions over time.

#### Criteria for discontinuing or modifying allocated interventions

Discontinuation of any stage of the trial for a particular participant will occur if the participant requests as such and/or if the participant, parent/legal guardian, researcher, or clinician deems that the intervention or participation in the trial is causing harm (e.g., emotional distress). Should this occur, the case will be discussed with the Data Monitoring Committee (DMC), who will determine whether there is sufficient concern to halt the study entirely.

#### Strategies to improve adherence to interventions and to promote participant retention

The compensation structure is set to $20 at baseline, with an additional $10 for completing each stage of EMA data collection with at least two thirds (i.e., 14 of 21) of the data points completed, which is designed to encourage data completeness and reduce attrition, in accordance with published recommendations for conducting EMA studies with youth [39]. Adherence will be monitored by examining rates of EMA completion, self-reported use of the data visualization platform, and data analytics of usage of the data visualization platform (anonymized and in aggregate). For participants who discontinue their participation, we will record the reason why.

#### Relevant concomitant care permitted or prohibited during the trial 

Participants will be encouraged to continue to engage in any other treatments for their chronic pain concurrently with trial participation. As the 3P approach to chronic pain management (combination of physical, psychological, and pharmacological therapies) is the standard of care, it was concluded to be unethical to stop or delay any of these treatments during the trial. Indeed, the intention of the data visualization intervention would be to supplement or support other therapies; therefore, the concurrent use of additional interventions was deemed to be the most ecologically valid and ethical approach. Participants will be asked to report the use of any concurrent interventions during the trial at baseline and during each feedback questionnaire.

Two additional measures have been put in place to provide support to participants during the trial. Resources for pain and mental health care are included on the consent and assent forms for participants to reference. Additionally, during EMA assessment periods, the participant will receive a prompt at the end of each day to try a free self-management application (*Rootd*; www.rootd.io). *Rootd*’s content is based on cognitive behavioral therapy and includes lessons on understanding and managing anxiety in the short and long term, a journal tool, exercises, and step-by-step guides to strategies such as deep breathing and active visualization. The app also features an emergency contact button to call a loved one or hotline if in distress and a Personal Stats Page to track user progress.

#### Provisions for post-trial care

No specific provisions have been made for post-trial care; participants will be encouraged to continue with their current treatment plan as directed by their care providers. However, should a participant express emotional distress in response to trial participation, either during or after the trial, they will be provided with mental health resources and referral suggestions, if appropriate (see the section below on adverse events).

